## **KEY WORDS**

**diabetes, well-being, target, feasibility, psychometric, glycaemic**

## STUDY FLOW CHART

[figure not shown]

Figure 1: flowchart demonstrating the feasibility study process and timeline

## **STUDY PROTOCOL: ATTAINS Study**

### **1 BACKGROUND**

For diabetes healthcare professionals, the importance of a personalised approach to management and goal-setting in people with diabetes has never been clearer, evidenced by the release of the joint ADA/EASD consensus statement (Davies et al., 2018). A diabetes treatment goal known to be important in predicting later health problems is average blood glucose (HbA1c). HbA1c tells us what the blood glucose of people with diabetes has been like over the past 8-12 weeks (Welsh, Kirkman and Sacks, 2016). Over time, HbA1c helps predict what the chances are of developing health problems later in life for someone with diabetes (World Health Organization, 1999). Chronically high HbA1c readings have been shown to negatively impact upon the physical health of people with diabetes: diabetes is one of the leading causes of adult blindness in the UK (Liew, Michaelides and Bunce, 2014), increases the risk of cancer (Noto et al., 2011, Ohkuma, Peters and Woodward, 2018) and dementia (Cheng et al., 2012, Chatterjee et al., 2016), more than doubles the risk of heart attack (NHS Digital, 2016), trebles the risk of stroke (NHS Digital, 2016) and is the commonest cause of end-stage renal failure (NHS Digital, 2016) and non-traumatic lower limb amputation in Europe (NHS Digital, 2016).

Several factors have a bearing on the achievement of glycaemic goals in people with diabetes (Ali et al., 2013). From a patient's perspective, lower levels of motivation and knowledge and higher levels of mental health comorbidity can create barriers to achieving optimal HbA1c levels (Khunti et al., 2018). From a healthcare perspective, contradictory guidelines and complex management options can cause confusion for clinicians. Underfunded NHS healthcare systems struggling to achieve national audit standards are often overwhelmed by the quantity and cost of diabetes-related healthcare interventions (Ali et al., 2013).

Although awareness of the importance of achieving glycaemic targets amongst patients with diabetes is improving with patient education (Berikai et al., 2007), many patients remain unaware of the preventable excess risk posed by inadequate HbA1c control. Despite many new pharmacological interventions that have become available in the past decade, achievement of HbA1c treatment targets in England and Wales has remained stubbornly below 30% for T1DM and below 70% for T2DM (NHS Digital, 2018). Evidence for lack of progress in the achievement of optimal glycaemic control is reflected in studies globally (Khunti et al., 2018). Outdated guidelines and national audit standards in England have limited progress towards the personalisation of diabetes care. People with diabetes have historically struggled to access evidenced-based diabetes education (though this is improving)

and negative patient perceptions on the intensification of diabetes treatment remain prevalent (O’Connor, Crabtree and Yanoshik, 1997, Grant et al., 2011, Khunti et al., 2018).

Awareness amongst healthcare professionals of the importance using treatment targets to drive improvement in micro- and macro-vascular outcomes is good. Compelling evidence on the use of personalised glycaemic treatment targets in response to patient factors is gaining traction amongst clinicians in primary and secondary care. Little evidence exists, however, on the long term impact that clinician-initiated glycaemic target-setting has on psychological and self-management abilities of patients. Further work is required.

The ATTAINS Study will look at the effect that A1c goal-setting has on the psychological well-being of people with diabetes. This is feasibility study to see if a bigger project is justified in the future. The psychological impact that HbA1c goal-setting has on people with diabetes is unknown. A better understanding of this could help people with diabetes achieve their A1c goals.

## **2 RATIONALE**

The current literature points to the clear reduction in the risk of the complications of diabetes by having individualised treatment targets (Diabetes Control and Complications Trial Research Group et al., 1993, Turner, 1998, UK Prospective Diabetes Study (UKPDS) Group, 1998, The ACCORD Study Group, 2008, Ismail-Beigi et al., 2011). There is minimal understanding of the psychological effect of treatment targets in people with diabetes.

Depending on individual patient factors, current local practice at STHK results in setting glycaemic targets that are either higher (more relaxed) or lower (more stringent) than patient’s current HbA1c readings. It is felt that studying the psychological impact of setting HbA1c targets in people with diabetes is essential. Risk assessments of higher and lower HbA1c target use are covered in [section 8.1](#), ‘Assessment and management of risk’.

The rationale for studying the use of explicit targets both above and below current HbA1c readings stems from current practice, testing whether “over-achievement” (i.e. the participants HbA1c being better than their target) or “under-achievement” have differing psychological implications.

In the planning of a large study, such as a randomised control trial, investigators draw upon many resources. This often includes past experience, findings from other studies and the views of patients and colleagues. Where uncertainties lie on the viability of a large study, preparatory studies are often needed (NIHR, 2016). The proposed feasibility study aims to see if it is feasible to undertake a larger trial in evaluating the psychological impact of HbA1c target-setting in people with diabetes.

### 3 THEORETICAL FRAMEWORK

This study will address the research questions using a mixed-methods approach, relying on both qualitative and quantitative techniques. As described succinctly by Johnson and Onwuegbuzie (2007), mixed methods research is “the class of research where the researcher mixes or combines quantitative and qualitative research techniques, methods, approaches, concepts or language into a single study or set of related studies.” Johnson et al. (2007) summarise mixed methods research as offering a “third methodological paradigm” alongside traditional qualitative and quantitative methods. This can help bring a richness to quantitative data and help to usefully triangulate qualitative data to produce research that becomes more than the sum of its parts (Johnson, Onwuegbuzie and Turner, 2007, Fielding, 2012). From the perspective of this research, employing a mixed method approach will bring greater real-world relevance to the data and will consequently produce findings that are meaningful for both patients and healthcare professionals. Applying methodological approaches using both qualitative and quantitative methodologies will bring enhancements to the overall project in excess of the sum of the original datasets, each addressing the limitations of the other.

Answering the research questions using quantitative feasibility outcomes defined by the NIHR (2016) and using semi-structured interviews in both people with diabetes and healthcare professionals, the findings can be triangulated to bring richness to the data and to help determine if this preliminary study justifies a larger study of this nature in the future. Semi-structured interviews will be carried out from a phenomenological (i.e. study of the participants’ lived experiences of the events in the study) perspective (Creswell and Poth, 2016) and analysed thematically using the framework method of data analysis (Gale et al., 2013).

From a quantitative perspective, alongside the primary outcomes of feasibility (rates of eligibility, recruitment, retention, response), preliminary data on the impact of A1c goal-setting has on the psychological well-being of people with diabetes will be gathered.

### 4 RESEARCH QUESTION/AIM(S)

1. What is the feasibility of undertaking a randomised control trial evaluating the effect of setting explicit glycaemic targets on psychometric and glycaemic outcomes in people with diabetes? **(Study A)**
2. What is the preliminary impact of setting explicit glycaemic targets above and below current HbA1c readings on psychometric and glycaemic outcomes in people with diabetes? **(Study A)**
3. What are the experiences, views and opinions of people with diabetes on the acceptability of the study processes and on glycaemic target-setting? **(Study B)**

4. What are the experiences, views and opinions of healthcare professionals on glycaemic target-setting and on the use of individualised treatment targets in people with diabetes? (**Study C**)
5. What are the experiences, views and opinions of people declining entry into study A on barriers to participation in diabetes research? (**Study D**)

#### **4.1 Objectives**

Using a mixed-methods approach, these related studies aim to explore:

1. the feasibility of evaluating the use of explicit glycaemic targets in people with diabetes.
2. the preliminary impact of setting explicit glycaemic targets on psychometric and glycaemic outcomes in people with diabetes.
3. the experiences, views and opinions of people with diabetes on the acceptability of study processes and glycaemic target-setting in the context of their diabetes care.
4. the experiences, views and opinions of diabetes healthcare professionals on the use of glycaemic target-setting and the individualisation of glycaemic targets in people with diabetes.
5. the experience, views and opinions of people declining entry into study A on barriers to participation in diabetes research.

## 5 STUDY DESIGN and METHODS of DATA COLLECTION AND DATA ANALYSIS

This is a mixed-methods study focussing on determining the feasibility of evaluating psychometric outcomes when setting explicit glycaemic targets in people with diabetes.

Quantitative data will be captured on feasibility outcomes and preliminary psychometric outcomes and the acceptability of the study intervention (**Study A**). Recruited participants will be surveyed on their perceived barriers to ongoing study participation.

Qualitative semi-structured interviews will obtain the experiences, views and opinions of people with diabetes (**Study B**) and healthcare professionals (**Study C**) on the study processes and the use of and impact of glycaemic target setting on the psychological well-being of people with diabetes.

Patients eligible for study A but declining participation will be asked if they would be willing to take part in a follow-up semi-structured interview study evaluating barriers to participation (**Study D**).

### 5.1 Study A

Design: Single-centre, parallel group, randomised feasibility study. This study will test the feasibility of conducting a randomised controlled trial (RCT) evaluating the psychometric impact of setting explicit glycaemic targets in people with diabetes (type 1 and type 2). There is deliberate separation of the initial clinic appointment (visit one; 0 months) and delivery of the intervention (visit two; 3 months) to allow for clinical care to be optimised and avoid conflict between the clinician advice and the study target. A short follow-up period 3 months post intervention has been selected to allow testing of feasibility outcomes and preliminary psychometric and glycaemic outcomes whilst minimising the health impact of the HbA1c target change to the participants.

Study Processes: people with diabetes meeting inclusion criteria and not excluded by exclusion criteria who are due to attend new patient diabetes clinic will be screened for entry into study A. Patients meeting eligibility criteria will be invited to entry into the study by postal letter with an included participant information sheet. Follow-up telephone calls will check patient interest and coordinate screening visits.

At visit one (0 months), invited patients will attend for a screening visit and informed consent process at the time of attendance to their diabetes clinic appointment. Those declining to take part will be

asked to complete a short survey evaluating barriers to participation (Barriers to Participation survey, [Section 11.1](#), Appendix 1). Baseline characteristics will be recorded: NHS number, age, sex, ethnicity, diabetes type, diabetes duration, postcode, point of care (POC) HbA1c, Blood Pressure (BP), BMI, educational status and prescribed glucose-lowering drugs. Participants will attend their usual diabetes clinic appointment for optimisation of their diabetes care. Participants will be randomised (stratified [strata: type 1 diabetes, type 2 diabetes]] random permuted block strategy) 1:1 into two groups using an online randomisation service (Altman and Bland, 1999, Suresh, 2011, Sealed Envelope Ltd, 2020).

At visit two (3 months), participants will visit to have a POC HbA1c reading and complete a series of validated baseline psychometric questionnaires (EQ-5D-5L – Health-related quality of life measure, SDSCA – Summary of Diabetes Self-Care Activities, PAID – Problem Areas in Diabetes, DES-LF – Diabetes Empowerment Scale, WBQ-12 – Well-being Questionnaire). The study intervention will be delivered as described using the TIDieR Checklist (Hoffmann et al., 2014):

- Intervention: Participants in group A are given an explicit HbA1c target 5mmol/mol above their current HbA1c reading. Participants in group B are given an explicit HbA1c target 5mmol/mol below their current HbA1c reading.
- Rationale: The feasibility of studying the use of glycaemic target-setting on psychometric outcomes in people with diabetes is unknown. Over-achievement and under-achievement of glycaemic targets has an unknown effect on psychometric outcomes and long term glycaemic control in people with diabetes.
- Materials: Participants will be provided with a sterilised, laminated leaflet (see Appendix 2) explaining in lay terms the rationale for HbA1c monitoring in diabetes. The leaflet will include a diagrammatic representation of their current HbA1c reading against their explicit target. A short scripted HbA1c summary will be read to participants by the researcher, along with an opportunity for participants to ask questions.
- Intervention provider: the intervention will be provided by the researcher employed by St Helens and Knowsley Teaching Hospitals NHS Trust. The researcher has a background working as a specialist trainee in diabetes and endocrinology and is fully trained in infection control measures, including precautions related to COVID-19.
- Mode of intervention delivery: the intervention will be provided face-to-face on an individual basis, following the latest UK government guidance on personal protective equipment and social distancing.
- Location: the intervention will be in a consultation room in the Diabetes Centre in St Helens Hospital.
- Time requirements/timing: the intervention will take place 3 months after study entry to allow for initial secondary care clinical management (undertaken at study entry) to be fully

established. Patients will attend the Diabetes Centre to complete a series of baseline questionnaires (30 minutes), a blood sample (10 minutes) and the intervention (5 minutes).

- Both the participants and researcher will be unmasked to intervention allocation. Clinical management of the patient will not be altered.

At visit 3 (6 months), participants will have a POC HbA1c reading and repeat the psychometric questionnaires. Participants will complete a study acceptability survey. Participants will attend their follow-up diabetes clinic appointment as normal to ensure optimal management is maintained. Glycaemic targets will be reset to the evidence-based appropriate target by the clinician. End of study A.

Data collection: A password-protected Microsoft Excel dataset template will be created for data collection purposes. The dataset master copy will be saved on an NHS-encrypted computer. Daily cloud backups are made to minimise data loss (see research data management plan). Data will be obtained from the following sources:

1. Eligibility/recruitment/retention/response rate data will be counted per participant and recorded.
2. Blood test POC HbA1c data will be captured from electronic patient records systems.
3. Baseline demographic data will be obtained firstly from electronic patient records systems and if unavailable, directly from the patient.
4. Physiological measurement (blood pressure, height, weight) will be obtained at participant visits.
5. Paper questionnaires will be completed by hand by study participants and subsequently inputted into the dataset by the study investigator.

Quality control of all equipment will be as per NHS standards.

Data storage: Key research data files containing any sensitive information (e.g. data collected) will be stored on an NHS-issued, encrypted, password-protected NHS laptop. Data will be stored via the laptop on NHS trust cloud storage associated with the PhD student's clinical research fellow post in the NHS. Therefore, if data were to be lost or become corrupt, for whatever reason, regular (daily) backups are accessible from the NHS trust network. The PhD student, [name], will be responsible for maintaining data storage, backups and security. Physical data (e.g. completed questionnaires, audio recording devices, consent forms) will be catalogued, filed securely and placed in a separate, locked room on NHS property within one day of receipt. Physical data will be accessed when required on the hospital site. Physical data will remain on-site until no longer required, at which point it will be destroyed. Patient identifiers will be held in a separate, password-protected database

and linked through a unique study code. Separation of patient identifiers from other data will be at the point of entry into the database.

Data analysis: Participant characteristics and feasibility outcomes will be reported with descriptive statistics, presenting continuous variables as means (standard deviation, SD) and categorical variables as numbers (%). For psychometric outcomes, paired baseline and endpoint data will be presented as mean differences (95% confidence interval, p-value). The paired two-tailed student's t-test will be used to compare means of parametric datasets (EQ-VAS index scores, PAID score, SDSCA scores, DES-LF scores, WBQ-12 scores). Differences between categorical variables will be analysed using the chi-squared test (EQ-5D-5L dimension responses). The Wilcoxon rank-sum test will be used to compare non-parametric data sets (EQ-5D-5L index scores). Correlations between different psychometric outcomes will be determined using spearman's rank correlation coefficient. Statistical methods will use SPSS v.25 statistics software (IBM Corp., 2017) and expert statistician input.

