## **7 SAMPLING AND RECRUITMENT**

### **7.1 Eligibility Criteria**

#### **7.1.1 Inclusion criteria**

Study A: All patients with poor glycaemic control (HbA1c 64 to 125 mmol/mol) aged  $\geq 18$  due to attend new patient clinic who are able to provide informed consent and have a confirmed diagnosis of diabetes mellitus (including Type 1 and Type 2) will be screened for entry into study A.

Study B: Patients enrolled in study A will be considered for inclusion in study B.

Study C: Healthcare professionals (including consultant, specialist nurse, nurse consultant, dietician, specialist registrar and specialty doctor grades) working at St Helens and Knowsley Teaching Hospital NHS Trust who are directly involved in the care of people with diabetes will be considered for inclusion in study C.

Study D: Eligible patients declining entry into study A will be approached for inclusion in study D.

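### Study A allocates participants at visit 1, three months before the baseline questionnaires and the intervention, with no stated reason and no rule concealing the allocation until visit 2

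*Protocol*

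**What the plan says.** Randomisation is described once in Section 5.1, within the visit 1 (0 months) account: "Participants will attend their usual diabetes clinic appointment for optimisation of their diabetes care. Participants will be randomised". The method is a stratified "random permuted block strategy) 1:1 into two groups using an online randomisation service", with diabetes type as the stratum.

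The next step is three months later: "At visit two (3 months), participants will visit to have a POC HbA1c reading and complete a series of validated baseline psychometric questionnaires". The target is set 5 mmol/mol above or below that visit's reading, and Section 5.1 confirms that "the intervention will take place 3 months after study entry". The reason given for the gap is that clinical care should settle first and clinic advice should not clash with the study target.

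On masking, the intervention description says: "Both the participants and researcher will be unmasked to intervention allocation. Clinical management of the patient will not be altered". It gives no time at which allocation becomes known.

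Appendix 2 lists the baseline questionnaires and the intervention under visit 2 and has no row for randomisation. The lay summary script in Appendix 1 has the HbA1c and questionnaires completed first at visit 2. The researcher then gives the target and tells the participant whether they are over- or under-achieving.

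Section 4.2 makes retention a primary outcome. Section 8.9 sets 80% retention at follow-up as a progression criterion, without saying from which visit it is counted.

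**The concern.** A baseline is protected from allocation only if it is measured before allocation, or while allocation is concealed. Neither is secured here. The psychometric outcomes are all self-reported, and Section 5.1 analyses them as paired change from visit 2 to visit 3. If knowledge of the arm affects visit 2 answers, the effect enters every change score. The researcher takes consent at visit 1 and delivers the intervention at visit 2, and may know the arm for the whole interval.

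The second consequence is loss in the gap. A participant who leaves between visits 1 and 2 has been randomised but has received nothing that differs by arm and contributes no pair. Such losses use up allocations and can disturb the balance that blocking within diabetes type was meant to give. If retention is counted from visit 1, they also sit in the same figure as losses after the target was given. A feasibility study tests the procedure that a main trial would inherit, so the order of these steps deserves to be settled now.

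**Working it through.** **Sequence as written.**

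| Step | Visit | Source |
|---|---|---|
| Consent | 1 (0 months) | Section 5.1; Appendix 2 |
| Clinic appointment | 1 | Section 5.1 |
| Randomisation | 1, in the sentence after the clinic appointment | Section 5.1; no row in Appendix 2 |
| HbA1c for the target, baseline questionnaires | 2 (3 months) | Section 5.1; Appendix 2 |
| Target given, group-specific message | 2, after the questionnaires | Appendix 1 script |
| Endpoint questionnaires | 3 (6 months) | Section 5.1; Appendix 2 |

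The stated reason for the gap explains why the intervention waits. It does not explain why allocation comes before the wait.

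**The plan's own figure.** Section 7.2.1 needs 72 eligible patients to enrol 50 at 70% participation. This reproduces: 0.70 × 72 = 50.4, and 50 / 0.70 = 71.4, rounded up to 72.

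**Effect of loss in the gap.** The protocol gives no loss rate between visits 1 and 2. Let d be that rate, assumed to be 5% to 20%; the upper end equals the total loss that Section 8.9 tolerates.

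- Under the current plan, the number with any baseline questionnaire is 50 × (1 − d).
- If the 80% criterion is counted from visit 1, it requires 0.80 × 50 = 40 at follow-up. The loss still allowed from visit 2 to visit 3 is 1 − 0.80 / (1 − d).
- To randomise 50 at visit 2, the number to consent is 50 / (1 − d), rounded up. The number of eligible patients is that divided by 0.70, rounded up.

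| Assumed d | Reach baseline, of 50 | Per arm | Visit 2–3 loss still allowed | Consent for 50 randomised at visit 2 | Eligible |
|---|---|---|---|---|---|
| 5% | 47.5 | 23.75 | 15.8% | 53 | 76 |
| 10% | 45 | 22.5 | 11.1% | 56 | 80 |
| 15% | 42.5 | 21.25 | 5.9% | 59 | 85 |
| 20% | 40 | 20 | 0% | 63 | 90 |

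**What a single retention figure hides.** With 50 enrolled, 8 lost before visit 2 and 2 after gives 40/50 = 80%, and 2 before and 8 after also gives 80%. Retention once a target has been given is 40/42 = 95% in the first case and 40/48 = 83% in the second. Losing 11 before visit 2 and none after gives 39/50 = 78%, which misses the criterion although everyone given a target stayed.

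**Whether the larger intake is reachable.** Section 8.9 forecasts 32 eligible and 22 enrolled per month over four months: 4 × 32 = 128 eligible and 4 × 22 = 88 enrolled. Both exceed the largest need in the table (90 and 63). The minimum green recruitment rate of 13 per month gives 4 × 13 = 52, just short of the 53 needed at 5% loss.

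**The case against.** The strongest reply is that the documents do not show anyone's answers being affected.

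- **Participants.** The unmasking statement sits in the description of the visit 2 intervention, and the Appendix 1 script reveals the target only after the questionnaires. Participants may well complete the baseline without knowing their arm. This stands as far as it goes. But the order of a script is not a concealment rule: it sets no time of disclosure and does not mask the researcher. The flow chart and the participant information sheets were not available for this review and might say more.
- **Researcher.** The questionnaires are completed by hand by the participant, and the investigator only enters them. Influence by the researcher is therefore possible, not documented. This also stands.
- **Retention.** Section 5.1 records retention per participant, so losses before and after the target can be tabulated whatever the date of randomisation. This is right. Moving randomisation does not define the 80% criterion; that needs its own sentence.
- **Concealment instead.** A statement that allocation stays hidden until the questionnaires are returned would protect the baseline without moving randomisation. It would not stop pre-target losses from being post-randomisation losses.

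A reader might also infer several stronger faults that the text does not support.

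- Clinic care at visit 1 was optimised with the arm known: the appointment is written before randomisation, Section 7.3.1 gives care to a clinician outside the research, and Section 5.1 says management will not change.
- Early dropout differs by arm: that needs participants to know their group, which is not stated.
- Baseline-adjusted analyses are biased: none is planned in this protocol.
- The HbA1c rules conflict: Section 7.1.1 ("All patients with poor glycaemic control (HbA1c 64 to 125 mmol/mol") applies at entry, while the target is defined from the visit 2 reading. These do different jobs and do not contradict each other.

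**Conclusion.** The point holds in a limited form. As written, allocation precedes the baseline questionnaires, the target-setting HbA1c and the intervention by about three months, in an open-label study, without a stated reason or a concealment rule. The scores labelled baseline are post-randomisation measures. Knowledge of the arm when they are taken is possible for the researcher and less likely, though not excluded, for the participant.

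No bias can be sized from the documents. The measurable cost is randomised participants who yield no pair: 2.5 to 10 of 50, if 5% to 20% are lost in the gap. That range is an assumption, and the retention figures assume counting from visit 1.

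The primary outcomes are feasibility measures and the psychometric results are preliminary, so this does not undermine the study. It is a specific, low-cost improvement, best made before recruitment because the order cannot be changed for participants already allocated.

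**What to change.** 1. In Section 5.1, keep consent at visit 1. Move the online randomisation to visit 2, after the HbA1c is recorded and the questionnaires are handed in, immediately before the target is given.
2. Add a randomisation row to Appendix 2 under visit 2.
3. In Sections 4.2 and 8.9, report retention separately for consent to visit 2 and for visit 2 to visit 3, and state the denominator of the 80% criterion.

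If there is a practical reason to allocate at visit 1, state it, and state that allocation stays concealed from participant, researcher and treating clinician until the visit 2 questionnaires are returned. This is second best, because losses in the gap remain post-randomisation losses.

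The service, the strata and the visits are unchanged. With 50 consented, about 40 to 48 would be randomised at the assumed 5% to 20% loss. The missing patients would give no paired data under the current plan either. To keep 50 randomised, Section 7.2.1 would need 53 to 63 consented and 76 to 90 eligible in place of 50 and 72. That fits the Section 8.9 forecast but not its minimum recruitment rate.
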